## Abstract

**Background:**

Evidence suggests inflammation may be a key mechanism by which psychosocial stress, including loneliness, predisposes to depression. Observational and clinical studies have suggested simvastatin, with its anti-inflammatory properties, may have a potential use in the treatment of depression. Previous experimental medicine trials investigating 7-day use of statins showed conflicting results, with simvastatin displaying a more positive effect on emotional processing compared with atorvastatin. It is possible that statins require longer administration in predisposed individuals before showing the expected positive effects on emotional processing.

**Aims:**

Here, we aim to test the neuropsychological effects of 28-day simvastatin administration versus placebo, in healthy volunteers at risk for depression owing to loneliness.

**Method:**

This is a remote experimental medicine study. One hundred participants across the UK will be recruited and randomised to either 28-day 20 mg simvastatin or placebo in a double-blind fashion. Before and after administration, participants will complete an online testing session involving tasks of emotional processing and reward learning, processes related to vulnerability to depression. Working memory will also be assessed and waking salivary cortisol samples will be collected. The primary outcome will be accuracy in identifying emotions in a facial expression recognition task, comparing the two groups across time.

Depression is common and associated with considerable health disability. Around a third of patients are resistant to current treatments.^1^ Thus, there is a pressing need to develop antidepressant medications with novel mechanisms of action or, conversely, to identify alternative pathophysiological pathways leading to depression that can be targeted with new treatments.^2^ A validated method to investigate this area is based on the cognitive neuropsychological model of depression.^3^ Both people with depression and those at risk for developing depression consistently show negative biases in emotional processing.^4–6^ This bias has been demonstrated reliably in tasks of facial expression recognition, memory and attention,^7–9^ and is thought to play a key role in the development and maintenance of clinical depressive symptoms.^10^ Acute antidepressant administration has been found to reduce these negative biases of emotional information in healthy controls and patients with depression.^11–13^ Further, early changes in these biases are associated with later antidepressant response.^14,15^ Reward learning has also been reported to be affected by depression and anhedonia, with depression found to be associated with both reduced sensitivity to reward and heightened sensitivity to loss.^16,17^ Antidepressants have been associated with enhanced reward learning,^18^ and specifically, reduced sensitivity to loss.^19^ Non-emotionally salient cognition such as working memory is also an associated impairment of depression,^10^ but, unlike emotional cognition, evidence that conventional antidepressants improve this symptom is conflicting.^20^

## Neuroinflammatory hypothesis of depression

Both emotional biases and impaired cognitive function have been associated with inflammation. For example, treatment with the proinflammatory cytokine interferon-α has been reported to induce a negative emotional bias, reduce motivation and increase anhedonia,^21,22^ and the induction of inflammation has been associated with working memory deficits in preclinical^23^ and human^24,25^ models.

There is a growing body of evidence supporting a neuroinflammatory hypothesis of depression.^26^ Raised inflammation and hypothalamic-pituitary-adrenal (HPA) axis hyperactivity are often associated, and are two of the most consistent biological findings in patients with depression.^27^ Multiple studies have shown that manipulating inflammatory pathways induces depression.^28^ HPA axis dysfunction and an elevated cortisol response to stress have also been associated with depression.^29^

Overall, an experimental medicine approach that explores the effects of medications with anti-inflammatory potential on measures of emotional processing, reward learning and working memory can provide valuable information before full-scale, randomised controlled trials to assess efficacy.

## Statins and neuropsychiatry

In recent years, there has been a significant interest in the investigation of the effects of statins in neuropsychiatric disorders, and especially depression.^30^ Statins are a class of medications usually prescribed to reduce peripheral cholesterol by inhibiting the liver enzyme 3-hydroxy-3-methylglutaryl coenzyme A reductase, with subsequent beneficial cardiometabolic effects.^31^ In addition, statins have widespread influences on neurobiological and immune systems and inflammatory pathways involved in depression pathophysiology.^32^ There are several examples of biological mechanisms that could support the antidepressant potential of statins.^32^ These include reduction of microglial and astrocyte activation, and inhibition of central cytokine release.^33–35^ Alternatively, *in vitro* studies have suggested 5-hydroxytryptamine 1a receptor dynamics are altered by statin-medicated cholesterol depletion.^36^ Because of their established safety profile, statins are ideal candidates for repurposing in the treatment of depression. However, inconsistencies between preclinical^37,38^ and clinical^37,39–43^ evidence mean that their role in the management of depressive disorders remains unclear. Such inconsistencies may be explained by differing study designs, including heterogeneous populations, interventions/exposures and outcomes of interest.^44^

## Loneliness, social isolation and the COVID-19 pandemic

It has been hypothesised that a raised baseline inflammatory load, in relation to risk factors such as age, comorbidities and adverse life events, could make certain people more likely to benefit from the anti-inflammatory and thus putative antidepressant effects of statins.^37^ In this context, the COVID-19 pandemic and its potential consequences on mental health^45^ highlight the need to be able to reduce the risk of developing depression fast and at scale. Social isolation and loneliness, both exacerbated by the measures needed to control the COVID-19 pandemic, have been associated with vulnerability to depression,^46^ possibly via a causal mechanism involving inflammation.^47,48^ The identification of strategies that may be protective against the negative mental health consequences of such psychosocial stressors would therefore have relevance on a large population scale.

An observational study carried out during the COVID-19 pandemic highlighted that, compared with several other medications (including antihypertensives), statin use was associated with less negative bias in tasks of emotional processing and lower sensitivity to loss in a reward processing task.^49^ These findings suggest that reducing inflammation via a statin could have a protective effect against depression in the context of the COVID-19 pandemic and its aftermath, at times of high levels of psychosocial stress such as social isolation and loneliness. We recently conducted a study in healthy participants showing that 7-day atorvastatin, compared with placebo, worsened emotional negative bias by increasing the identification of fearful facial expressions; this occurred independently from subjective states of mood, anxiety and peripheral markers of inflammation.^50^ Seven-day simvastatin, on the other hand, was associated with some evidence of improvement in negative bias (i.e. more positively valenced intrusions in emotional recall), but also with an increase in subjective scores of anxiety compared with controls.^51^ Compared with atorvastatin, simvastatin is a more lipophilic molecule, and is therefore more capable of crossing the blood–brain barrier and potentially expressing an effect in the central nervous system.^52^ Clinical evidence suggests a stronger antidepressant potential of the more lipophilic simvastatin compared with atorvastatin.^39,41,53^ Neither study found any effect of statins on reward learning or non-emotional cognition.^50,51^ Findings from these latter experimental medicine trials^50,51^ seem to differ from the earlier observational study.^49^ Moreover, they do not appear in keeping with the possible antidepressant effect of statins seen in clinical populations.^37^ A possible explanation is that, although changes in emotional processing mechanisms can be seen after 7 days, the intricate pharmacological properties of statins^32^ means that they may require longer administration in predisposed (i.e. at risk for depression) individuals before showing the expected positive effects on emotional processing and reward learning,^49–51^ and, following that, on mood and anxiety.^37^

To verify this hypothesis, we designed the current experimental medicine trial: the Oxford Study of Simvastatin and Emotional Processing (OxSTEP). This study will assess the effects of 28-day simvastatin administration versus placebo on emotional processing, reward learning, working memory and waking salivary cortisol in people who are at risk for depression because of high levels of loneliness.

## Objectives and hypothesis

### Primary objective

The primary aim of this study is to test the neuropsychological effects of statins by assessing the effect of 28-day administration of statin treatment on emotional processing, reward learning and working memory compared with placebo, in healthy volunteers at risk for depression owing to loneliness.

### Secondary objectives

Our secondary objectives include using waking salivary cortisol as an index of HPA axis activation, indicating biological stress and arousal; collecting mood and anxiety questionnaires to examine if any underlying changes in emotional processing correlates with subjective measures; and looking at the effect of statin administration within specific subgroups.

Our prediction is that, relative to placebo, in this group of participants at risk for depression because of high levels of loneliness, 28-day simvastatin use will lead to positive effects on emotional processing (decreased negative bias), reward learning (increased sensitivity to reward versus loss) and working memory (increased accuracy on the N-back test) compared with placebo, as well as lowering waking salivary cortisol concentrations.

## Method

### Study setting

OxSTEP is an online, double-blind, parallel-group, randomised, gender-stratified, placebo-controlled experimental medicine trial. One hundred participants from across the UK will be recruited through online advertising. Researchers are based in the Department of Psychiatry at the University of Oxford. Participant enrolment started in July 2021 and is expected to end in March 2023. All data remains blinded at the point of submission.

### Sample size calculation

The sample size calculation was based on our primary outcome of accuracy on the facial expression recognition task, part of the Oxford Emotional Test Battery, a validated tool to assess emotional processing.^11,54,55^ We initially computed that a sample size of 25 per study arm would give 0.9 power to detect changes of the magnitude of those we have seen in a previous key study (drug mean 10.64 (s.d. 9.77) versus placebo mean 3.36 (s.d. 5.96)^12^). However, it is possible that online testing will have a reduced sensitivity to change in emotional processing compared with face-to-face testing in a laboratory. Additionally, a smaller magnitude of change would still be a clinically important difference that we would want to detect. For this reason, we have planned to recruit 50 participants per arm; this is made possible by the increased efficiency of online testing in participant recruitment.

### Recruitment

After responding to an online advert, potential participants will be shown the Participant Information Sheet and asked to complete a short online pre-screening form, comprising a brief questionnaire referring to the main inclusion/exclusion criteria, including the UCLA 3-item Loneliness Scale^56^ to assess for baseline loneliness level. Those who preliminarily appear to meet the inclusion criteria will be invited to a pre-screening telephone call with a researcher, where key criteria will be confirmed and informed consent explained. After participants have given online informed consent, they will have a screening session via video call with a study psychiatrist. During the screening, consent will be re-checked and information will be taken about medical history, concomitant medication, psychiatric history and current psychiatric symptoms using the Structured Clinical Interview for DSM-5 (SCID-5).^57^ Inclusion and exclusion criteria are reported in Table 1. A score of 6 or more on the UCLA 3-item Loneliness Scale indicates moderate to severe loneliness, and is a conservative assessment of the risk of depression.^58^ The three-item scale correlates well with the more comprehensive Revised UCLA Loneliness Scale.^56,59^ Other eligibility criteria have been chosen to (a) recruit a healthy adult population, for whom it would be safe to take the medication without significant clinical oversight; and (b) limit extreme cognitive and clinical heterogeneity.

**Table 1 tab01:** Participant eligibility criteria

Participant eligibility criteria
Inclusion criteria
Male or female
Aged 21–65 years
At risk for depression as measured by a score ≥6 on the UCLA 3-item Loneliness Scale
Body mass index in the range of 18–30 kg/m^2^
Willing and able to give informed consent for participation in the study
Registered with a general practice and consent to their general practitioner being informed of participation in the study
Currently living in the UK and sufficiently fluent in English to understand and complete the tasks
Able to access and use a computer with internet
Able to complete online questionnaires and tasks
Exclusion criteria
Currently on any regular prescribed medications (except the contraceptive pill), unless unlikely to compromise safety or affect data quality in the opinion of the investigator
History or current significant psychiatric illness (other than past (>6 months) episodes of depression or anxiety)
Current alcohol or substance misuse disorder (<6 months)
History of, or current significant hepatic disease
History of, or current significant neurological condition (e.g. epilepsy)
History of haemorrhagic stroke or deep brain structure stroke
Known hyperglycaemia/prediabetes/diabetes
Known hypersensitivity to the study drug (i.e. simvastatin) or sucrose
Pregnant, breast feeding or women of child-bearing potential who are not using appropriate contraceptive measures
Participation in a study that uses the same or similar computer tasks (apart from the N-back task) as those used in the present study
Participation in a study that involves the use of a medication within the past 3 months

We aim to minimise the number of participants lost to follow-up by respecting participants commitments outside of the study and working flexibly around them, regularly checking in with participants to keep them on track and engaged. Such flexibility is made possible by the innovative remote design of this study. Participants will be given a contact number and advised to get in contact if they have any concerns or their health status changes. If necessary, the researcher will contact the study medic. A participant will be discontinued from the study and advised to stop taking the study medication if deemed necessary by the medical lead. Withdrawn participants will be replaced and their data will not be included in the analysis.

### Randomisation

Using online randomisation tool Sealed Envelope version 1 (Sealed Envelope Ltd, London, UK; https://www.sealedenvelope.com/simple-randomiser/v1/lists), an uninvolved researcher will generate a randomisation code in blocks of four, stratified by gender, which will be stored in a sealed envelope in a lockable cabinet. Eligible participants will be randomised to receive either simvastatin 20 mg (50 participants) or placebo (50 participants). A dose of 20 mg is safe^60^ and has been successfully used in trials on depression in the past.^61^ Randomisation will occur up to a maximum of 4 weeks after screening, by one of the study researchers. Participants will be posted 30 days of the allocated drug/placebo to their address, as well as full written instructions of how and when to take them, and secure pre-paid postal boxes to return their saliva samples. Both the participants and the study researchers will be blinded to the study medication.

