#### Analysis

Demographic and baseline measures will be reported descriptively. Loneliness, mood, anxiety, side-effects and salivary cortisol measures will be analysed using repeated measures analysis of variance (ANOVA), with group (simvastatin versus placebo) as the between-participants factor and time (baseline versus final day session) as the within-participant factor. Feasibility outcomes for the remote design will be reported, such as drop-out rate, within-study exclusions, adherence and missing data rates.

Data distributions will be visually checked for all neuropsychological tasks, using boxplots. Extreme outliers (i.e. data values lying more than three times outside the interquartile range) will be excluded. The resulting data will be analysed with ANOVA, with group as the between-participants factor and time as a within-participant factor. The individual tasks will be analysed with the following additional within-participant factors: for FERT, emotion; for ECAT and EREC, valence; for PILT, win or loss; and for N-back, trial condition.

On the basis of potentially diverse pathophysiological effects of simvastatin, we will further explore the main outcomes (FERT accuracy, misclassifications, reaction times) in specific subgroups of participants (females versus males, age 21–40 *v.* 41–65 years, body mass index 18–25 kg/m^2^ (normal weight) *v.* 26–30 kg/m^2^ (overweight), self-report of family history of mental disorder positive versus negative). These subgroups will be added as between-participants variables in our ANOVAs. *Post hoc* sensitivity analysis to account for oral contraceptive pill use will be carried out.

Any significant interactions will be followed up using simple main effect analyses. When assumptions of equality of variances are not fulfilled, the Greenhouse–Geisser procedure^78^ will be used to correct the degrees of freedom.

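### Randomisation is stratified by gender, but the main ANOVAs leave gender out; the cost to the primary group × time test is nil to slight, and the remedy needs a gender × time term

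*Protocol article*

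**What the plan says.** The Study setting section of the protocol article describes a "double-blind, parallel-group, randomised, gender-stratified, placebo-controlled experimental medicine trial". The Randomisation section has the list-holder "generate a randomisation code in blocks of four, stratified by gender", with 50 participants intended per arm. No other stratification factor is named.

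The Analysis section sets out the main models:

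- Loneliness, mood, anxiety, side-effects and cortisol: repeated measures ANOVA "with group (simvastatin versus placebo) as the between-participants factor and time (baseline versus final day session) as the within-participant factor".
- Neuropsychological tasks, including the primary outcome: "The resulting data will be analysed with ANOVA, with group as the between-participants factor and time as a within-participant factor".
- Task-specific additions, all within-participant: "for FERT, emotion; for ECAT and EREC, valence; for PILT, win or loss; and for N-back, trial condition".

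Gender enters at one place only. Females versus males is one of four exploratory subgroup splits for the facial expression recognition task (FERT: accuracy, misclassifications and reaction times), and "These subgroups will be added as between-participants variables in our ANOVAs". The Method part of the Abstract defines the primary outcome as FERT accuracy compared between the arms over time, so the primary contrast is group × time.

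**The concern.** Blocking within gender forces the arms to be nearly equal on gender, so differences between the genders cannot contribute to the difference between the arms. A model without gender still counts those differences as error. Where gender predicts the quantity being tested, the standard error is then too large and the test conservative. The stake is some lost power and p-values that do not match the design.

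The Analysis section names the between-participants factor explicitly, so this is a stated choice rather than a detail left to a fuller document. How much it matters depends on which contrast is tested, and that has to be worked out.

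**Working it through.** **1. The plan's own figure.** The Sample size calculation section gives means of 10.64 and 3.36, SDs of 9.77 and 5.96, and 25 per arm for 0.9 power. Alpha is not stated; 0.05 two-sided is assumed.

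- Difference: 10.64 − 3.36 = 7.28. Pooled SD: √[(9.77² + 5.96²)/2] = 8.09.
- Normal approximation: n = 2(1.960 + 1.282)² × 8.09²/7.28², which rounds up to 26 per arm. Power at 25 per arm is 0.889.

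The stated figure reproduces to within one participant per arm and about one point of power. It involves no gender term, so the sample size is not affected by this point.

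**2. Inputs assumed.** The article gives no gender effect and no correlation between sessions. The unit is the within-gender SD of one session's score, and the correlation between baseline and final session is set at 0.5. The algebra takes equal numbers of each gender.

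**3. Group × time.** With two sessions this is the two-sample test on change.

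- Variance of change = 2(1 − 0.5) = 1.00.
- A stable gender difference is in both sessions and subtracts out, so it adds nothing.
- A gender difference *b* in change adds *b*²/4 to the error if gender is omitted. For *b* = 0.25, 1 + 0.0156 = 1.016; for *b* = 0.5, 1 + 0.0625 = 1.0625.
- The standard error is overstated by √1.0156 = 1.008 and √1.0625 = 1.031. Approximate type I error is 2[1 − Φ(1.96 × ratio)] = 0.048 and 0.043.

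**4. Group main effect.** This rests on each participant's average of the two sessions.

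- Variance = (1 + 0.5)/2 = 0.75.
- A gender level difference *a* adds *a*²/4. For *a* = 0.5, 0.8125; for *a* = 1, 1.00.
- The standard error is overstated by √(0.8125/0.75) = 1.041 and √(1/0.75) = 1.155. Approximate type I error is 0.041 and 0.024.

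**5. Simulation.** There were 20,000 trials per scenario, with n = 100, complete blocks of four within gender (52 and 48) and two-sided 0.05. Power is for a treatment effect of 0.57 SD at the final session, close to the 0.566 SD detectable with 80% power at 50 per arm. The Monte Carlo error of a 0.05 rate is √(0.05 × 0.95/20,000) = 0.0015. Each cell shows gender omitted / gender included.

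| Contrast | Assumed gender effect | Error variance | Type I error | Power, % |
|---|---|---|---|---|
| Group × time | level, 0.5 SD | 1.00 / 1.00 | 0.051 / 0.051 | 80.4 / 80.4 |
| Group × time | level, 1 SD | 1.00 / 1.00 | 0.050 / 0.050 | 80.7 / 80.7 |
| Group × time | change, 0.25 SD* | 1.02 / 1.00 | 0.049 / 0.051 | 79.9 / 80.3 |
| Group × time | change, 0.5 SD* | 1.06 / 1.00 | 0.045 / 0.052 | 78.5 / 80.3 |
| Group main effect | level, 0.5 SD | 0.81 / 0.75 | 0.040 / 0.050 | 33.3 / 36.4 |
| Group main effect | level, 1 SD | 1.00 / 0.75 | 0.024 / 0.052 | 25.9 / 36.9 |

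*With a level difference of 0.5 SD as well, which does not affect this contrast.

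The simulation agrees with the algebra.

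**6. Which term does the work.** In a repeated measures ANOVA a gender main effect enters only the between-participants error. Group × time is tested against the within-participant error, which a gender main effect leaves unchanged. The gender-included figures for group × time come from regressing change on group and gender, which amounts to a gender × time term. Error degrees of freedom fall from 98 to 97. For a task factor with *k* levels, the corresponding three-way error falls from 98(*k* − 1) to 97(*k* − 1).

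**The case against.** The strongest reply is that the planned comparison is between arms over time, and there each participant's baseline removes any stable gender difference. A reader might infer from the omission that standard errors are too wide for every outcome related to gender. The documents do not support that: the first two rows of the table show no effect at all, and a loss arises only if gender alters change over time. The larger losses belong to the group main effect, which averages in a pre-treatment session and is not the stated primary comparison. This part of the reply stands.

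It may also be said that gender is already in the exploratory FERT models. That is true, but those models cover one task, carry subgroup status and do not replace the main analysis.

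Two other inferences are tempting. One is that the omission inflates false positives or biases the treatment effect. It does neither, since blocking within gender balances the arms and the error is conservative. The other is that replacing withdrawn participants and excluding outliers or protocol deviators will upset the gender balance and so confound the result. Nothing in the article suggests that exclusions depend on gender and arm together, and a stable gender difference would still cancel in group × time. Those exclusions are a separate matter that a gender term does not cure.

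The mismatch between design and model remains. Nor can a gender difference in change be dismissed, because the Analysis section itself explores the sexes separately on the ground that simvastatin may act differently in different participants.

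**Conclusion.** The point holds in limited form. The main ANOVAs do not reflect the gender stratification, and the article gives no reason for leaving it out. The consequence for the primary group × time test ranges from none to slight, at most about 1.8 points of power over the range examined. It is larger, about 3 to 11 points, for the between-participants group effect. These sizes rest on assumed gender effects, a between-session correlation of 0.5 and near-equal numbers of each gender. The matter is minor to moderate: an inexpensive improvement that aligns the analysis with the design, not a threat to the validity of the result.

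**What to change.** Add a sentence to the Analysis section, before unblinding, along these lines: *every main between-arm ANOVA includes gender, the randomisation stratum, as a between-participants term with its interaction with time and, for the tasks, its interactions with the task's within-participant factor and with that factor and time together; group × gender terms are fitted only in the exploratory subgroup analysis.*

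The interactions must be written out. Adding gender as a main effect alone would leave the primary test exactly as it is. The exclusion of group × gender terms should also be explicit, because repeated measures routines often add every interaction between the between-participants factors by default.

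The cost is about one error degree of freedom per contrast, using a variable already held for randomisation. The sample size need not change.
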